## Abstract

**Background:**

Frailty is a complex multi-dimensional state of increased vulnerability to adverse outcomes and is associated with older age but there is growing evidence of accelerated ageing and frailty in non-geriatric populations, including those experiencing socio-economic deprivation and extreme social exclusion, such as people experiencing homelessness. Addiction, as a coping mechanism for prior trauma, is common among people who are homeless and can have a gendered dimension. Women experiencing homelessness and addiction have unique needs which require a gendered approach. The aim of this study is to evaluate the feasibility and impact of an exercise intervention to target the known physical functioning deficits and frailty which this population experiences.

**Methods:**

This quantitatively driven, sequential single-arm mixed-methods feasibility study will evaluate the feasibility and impact of a low threshold trauma informed exercise intervention on physical functioning and frailty in women experiencing homelessness and addiction. Physical function (10m Walk Test, 2Min Walk Test, Single Leg Stance, Chair Stand Test, hand grip dynamometry), frailty (Clinical Frailty Scale and the SHARE-Frailty Instrument) and nutritional status (Mini-Nutritional Status), pain (Numerical Rating Scale) and quality of life (SF 12-V2) will be evaluated. The 10-week intervention will involve a 3-times weekly exercise programme with protein supplementation. Following this, qualitative interviews, which will be thematically analysed using Braun & Clarke methodology, will be conducted. This study will be conducted in Dublin from February to July 2024.

**Discussion:**

Little is known about frailty-focussed interventions in women experiencing homelessness and addiction. This proposed study will help to increase the knowledge base regarding the physical health burden and frailty experienced by this vulnerable population and will deliver a targeted intervention with a gendered dimension to mitigate its affects. The findings of this research will help narrow the research gap and will guide clinicians and policy makers to implement unique gender-based treatment strategies for this population. (300).

**Clinical trials.gov number:**

NCT05700305.

## Introduction

The world’s population is ageing rapidly [1]. Frailty, a sometimes-preventable consequence of a rapidly ageing population, is a complex state of cumulative decline across multiple physiological systems which renders a person vulnerable to adverse health outcomes and greatly challenges healthcare systems [2]. Targeted interventions to manage frailty in older adults are recommended and exercise with nutritional supplementation has proven effectiveness in combatting and mitigating frailty [3–5].

Frailty as a construct is a geriatric concept which is strongly associated with increasing age [6]. Notwithstanding that biological age is closely linked to frailty, it is known that chronological age alone will not identify frailty as the health and functional life status of populations are so variable [7]. Growing evidence indicates the prevalence of premature ageing and frailty in non-geriatric populations [8, 9]. ‘Younger frailty’ has been identified in populations of lower socioeconomic status, who live in areas of greater deprivation and experience an earlier onset of illness and disability [10, 11]. In a study investigating people experiencing homelessness (PEH) admitted for inpatient care, 83% of participants had mobility problems and 70% were frail or pre-frail despite a low median age of 45 years [12, 13]. In an analysis of UK Biobank participants aged 37–73 years, 42% of individuals living with frailty were within the most socially deprived quintile of the cohort [10]. Females are known to experience higher levels of frailty compared to males [14, 15]. It is therefore not surprising that poor physical functioning and frailty is experienced by young women who are homeless and use drugs [16, 17].

Health services for PEH frequently focus on crisis-based medical, nursing and addiction services, often with a gender-blind lens [18, 19]. High levels of stigma, shame and fear result in women accessing services even less and seeking help at breaking point with complex coinciding physical and mental health needs [20, 21]. Homelessness and substance use in women is inter-sectoral and may overlap with trauma, abuse, domestic and sexual violence and exploitation, and the needs of these women are complex and unique [22]. Pathways into homelessness are frequently different to that of men and require a different approach [23]. Internationally, gender-based services for women who are experiencing homelessness and addiction are lacking and services are mostly delivered in mixed gender settings [18, 19]. Women-specific services are recommended to increase safety, stability, wellbeing, and psychosocial functioning to respond meaningfully to the serious health and social care needs of women in this setting [24]. Gender specific and gender sensitive research is required to fill this knowledge gap [25].

Our prior research, the LEAP-I study demonstrated high retention (83% female v 42% males) with excellent engagement and feedback from its female participants, yet caution was observed around engaging in a mixed exercised programme with men [16]. Women have traditionally been underserved in research and policy, yet multiple sources cite women as the fastest growing homeless demographic [23]. No study has examined how targeted women-only exercise programmes with nutritional supplementation work in practice in this population.

The overall aim of this study is to evaluate the feasibility and impact of exercise with protein supplementation, delivered with a low threshold and trauma informed approach, on physical functioning and frailty outcomes in a group of (non-geriatric) women experiencing homelessness and addiction challenges, through the delivery of an exercise intervention, followed by qualitative interviews. The objectives are:

To evaluate recruitment, retention and adherence rates, and any adverse effects of the intervention.To evaluate pre- and post-intervention levels of physical function, nutritional and frailty status, pain, and general health status.To evaluate programme feedback and gain deeper insights into participants perspectives and experiences of the exercise intervention.

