### Secondary outcomes

Secondary outcomes will measure physical function, frailty and nutritional status, pain and self-reported health status using a broad test battery outlined in Table 2.

**Table 2 pone.0300412.t002:** Test battery.

Construct Measured	Test
Sarcopenia and upper limb strength	Upper/Lower Limb circumference Hand grip dynamometry [27, 28]
Lower limb strength and endurance	30-sec Chair Stand Test [29]
Endurance and functional mobility	2-minute walk test [30]
Gait Speed	10m walk test [31]
Balance	Single leg stance [32]
Frailty	SHARE-FI [33], Clinical Frailty Scale [6]
Nutritional Status	Mini-Nutritional Assessment [34, 35]
Pain	Numerical Pain Rating Scale [36]
Health status/Quality of Life	Short Form 12 [37]

**1. Strength and muscular mass:** Muscle strength will be measured, using a Jamar Digital Hand Dynamometer, while sitting with the elbow flexed at 90°, the forearm mid-prone, the wrist in neutral and the hand unsupported [27, 28]. Results will be compared to normative reference values [38]. Two measurements will be recorded and also used for the SHARE-Frailty Instrument (FI) assessment [33].

Mid-calf circumference girth will be evaluated as this measure correlates with appendicular muscular mass [39]. This will be measured using a flexible tape measure at the level of the largest circumference of the calf. Measurements will be compared to gendered cut-off values [40]. Mid-arm muscle circumference reflects both muscle mass and caloric and protein adequacy and may be used to signify wasting or malnutrition [41]. This test has been recommended in situations where lower limb swelling is present [42]. The maximum upper arm muscular mass will be measured using a flexible tape measure. These results will be compared to global reference values [43].

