#### Sample size

A sample size calculation was conducted on the statistical package R, based on an expected adherence of 60%, a minimal acceptable adherence of 45% and a power of 80%, which indicated that a target sample size of 68 would be required. Due to the novelty of this study, the challenges of recruitment in this ‘hard to reach’ population and the feasibility focus of this study, while 68 will be the recruitment target, a minimal of 24 will be sought [53].

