## Data collection and management

### Analytic plan

All data will be pseudonymised at point of entry into excel spreadsheets and then transferred into IBM SPSS V28 for analysis. For quantitative data, nominal or ordinal variables will be reported as frequencies and percentages. Continuous variables will be summarised as mean and standard deviation if normally distributed and median and inter-quartile range if non-normally distributed. Data will be tested for normality using the Kolmogorov–Smirnov/Shapiro Wilk test and will be compared across timepoints using the general linear model procedure (normally distributed data) and the Friedman’s test (non-normally distributed data). Chi-squared t-tests will be used where appropriate and some data may be categorised to investigate relationships between variables. Exploratory regression models will be developed to explore correlates and predictors of frailty and poor physical functioning. For the qualitative data, Braun and Clarke thematic analysis methodology will be employed to provide an in-depth analysis of the exit interview data [50]. A *p*-value of <0.05 will be considered significant. To account for multiple comparisons, we will apply a Bonferroni correction by dividing the significance level by the number of tests conducted.

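### Objective 2 should be answered by the within-woman change with a 95% interval: near the accepted minimum of 24 women, Bonferroni-corrected p-values over at least 13 measures say little about impact

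*Protocol article*

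**What the plan says.** The Introduction sets the aim: "The overall aim of this study is to evaluate the feasibility and impact of exercise with protein supplementation". Its second objective is "To evaluate pre- and post-intervention levels of physical function, nutritional and frailty status, pain, and general health status". Under Secondary outcomes, these constructs are measured "using a broad test battery outlined in Table 2".

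The Analytic plan gives frequencies and percentages for nominal and ordinal variables, and mean with SD or median with IQR for continuous ones. Timepoints are compared by a general linear model if data are normal and by Friedman's test if not. On inference it says "A *p*-value of <0.05 will be considered significant" and then "To account for multiple comparisons, we will apply a Bonferroni correction by dividing the significance level by the number of tests conducted". It does not fix the number of tests, and it also foresees chi-squared tests and exploratory regressions.

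The Sample size section works from adherence only: "based on an expected adherence of 60%, a minimal acceptable adherence of 45% and a power of 80" per cent, "which indicated that a target sample size of 68 would be required". It then adds that "while 68 will be the recruitment target, a minimal of 24 will be sought". The article gives no effect size or SD for any functional or frailty measure, and singles out none of them as the main measure of impact.

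**The concern.** The only inferential rule stated for the impact half of the aim is a corrected significance threshold. That threshold becomes stricter with every test run, and it is applied to outcomes that played no part in sizing the study. With about 24 women, a real and moderate improvement in function or frailty could well fall short of it. A reader of the results would then be inclined to conclude that nothing changed.

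A feasibility study can say more than this from the same data: how large the paired change was, and how precisely it was estimated. The listed summaries do not supply that by themselves. The SD at each timepoint does not give the SD of the change, which also depends on the correlation between the two measurements. Friedman's test returns a p-value without an estimate.

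**Working it through.** **1. The plan's own figure.** Inputs from the Sample size section: p0 = 0.45, p1 = 0.60, power 80%. Alpha and sidedness are not stated there. For a one-sample proportion:

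n = (z_α·√(p0·q0) + z_β·√(p1·q1))² / (p1 − p0)²

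With one-sided α = 0.05: (1.645 × 0.4975 + 0.842 × 0.4899)² / 0.15² = 67.3, rounded up to 68. The target reproduces, and no secondary outcome enters it. (Two-sided α = 0.05 would give 86.)

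**2. Number of tests.** Counting each measure once under Secondary outcomes gives 13: grip, calf girth, mid-arm girth, chair stand, 2-minute walk, 10 m walk, single leg stance, SHARE-FI, Clinical Frailty Scale, MNA, pain NRS, PCS12 and MCS12. This is a count from the text, not a figure in it. Single leg stance is done on each leg, so 14 is also possible. The threshold is 0.05/13 = 0.00385.

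**3. Completers.** The Introduction reports 83% retention of women in LEAP-I. Using it only to set a range: 0.83 × 24 ≈ 20 and 0.83 × 68 ≈ 56. It is not a planning figure of this study.

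**4. Power.** A two-sided paired t-test stands in for the two-timepoint general linear model. With d the true change in SDs of the paired difference (assumed; the article gives none), power = P(T > t_crit), where T is non-central t with n − 1 degrees of freedom and non-centrality d√n. For n = 20 and d = 0.5, t_crit = 3.29 and the non-centrality is 2.24, which gives 19%.

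| Completers | d = 0.5, corrected | d = 0.5, uncorrected | d = 0.3, corrected | 95% CI half-width (SD of difference) |
|---|---|---|---|---|
| 20 | 19% | 56% | 5% | 0.47 |
| 24 | 25% | 65% | 6% | 0.42 |
| 38 | about 50% | 85% | 13% | 0.33 |
| 56 | 76% | 96% | 23% | 0.27 |
| 68 | 86% | 98% | 31% | 0.24 |

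The half-width is t(0.975, n − 1)/√n; for n = 24 it is 2.069/4.899 = 0.42.

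**5. More tests.** If 20 tests are run, power for d = 0.5 falls to 21% at n = 24 and 83% at n = 68.

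**6. Sensitivity to the effect scale.** A change of 0.5 between-woman SD equals 0.5/√(2(1 − r)) SDs of the difference, where r is the pre-post correlation and the SD is taken as equal at both times. All values of r are assumptions.

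| r | d | Power at n = 20 | Power at n = 24 |
|---|---|---|---|
| 0.5 | 0.50 | 19% | 25% |
| 0.7 | 0.65 | 38% | 50% |
| 0.8 | 0.79 | 60% | 74% |

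**The case against.** The case for leaving the plan alone has real weight.

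- Feasibility is the primary outcome, so sizing on adherence and leaving secondary outcomes unpowered is normal practice.
- Bonferroni is a valid method. In a single-arm study with many pre-post comparisons, strict error control guards against false claims of benefit.
- A general linear model of pre-post data can yield a mean change and its interval, and an article may leave the listing of such output to the full plan. A reader might infer that the size of change will not be estimated. The text does not support that; it shows only that the estimate is not made the readout.
- A reader might also infer that moderate changes will usually be missed whatever the recruitment. The figures contradict this: at the target, a 0.5 SD change is detected with 76% to 86% power.
- The effect scale is an assumption. With a high pre-post correlation, power is respectable even at 24.
- Nothing in the article says that non-significance will be taken as no change, or that a later trial will be sized from these data.

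All of these points stand, and they limit the concern to small numbers and smaller changes. They do not remove it: the minimum of 24 and the correction rule are both written into the plan, and together they leave corrected significance a weak guide to impact if recruitment is low. The non-normal route through Friedman's test still offers no estimate.

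**Conclusion.** The point holds in a limited form, as a worthwhile improvement in how objective 2 is read out. Under the assumptions of 13 tests and a true change of 0.5 SD of the paired differences, a corrected test misses that change in about 81% of studies with 20 completers and 75% with 24. The balance tips at about 38 completers. For 0.3 SD the change is missed in 69% of studies even with all 68 women measured twice. In those situations a corrected non-significant result says little about whether function or frailty changed, whereas an interval of about ±0.42 SD at 24 women shows what the data can and cannot exclude.

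The result rests on the assumed effect size and on the count of 13. A higher pre-post correlation would raise power and more tests would lower it. Ordinal scales and Friedman's test may do worse than the paired t-test used here. The primary feasibility outcome is not affected.

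**What to change.** Add to the Analytic plan that objective 2 is answered, for each secondary outcome, as follows:

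- **Continuous measures:** mean within-woman change with 95% CI and the SD of change.
- **Skewed measures:** median within-woman change with 95% CI.
- **Ordinal categories** (such as the Clinical Frailty Scale and the SHARE-FI category): proportions improving and worsening, each with 95% CI.

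State also that a non-significant corrected p-value will not be interpreted as absence of impact. Bonferroni-corrected p-values may be kept as a secondary output.

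The cost is a few sentences and somewhat more reporting, from data already being collected. The trade-off is less weight on significance claims for secondary outcomes, which the study was not sized to support.

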## Materials and methods

### Study design, setting and time frame

This single-arm quantitatively driven, sequential mixed-methods feasibility study will take place in Jane’s Place, Merchants Quay Ireland (MQI), a five day per week drop-in day-service centre in Dublin city centre, which provides medical and support services for socially excluded women who are homeless and/or in addiction. Following the intervention qualitative research in the form of individual exit interviews will be conducted with 20 participants. This study has received ethical approval from the Faculty of Health Sciences, Trinity College Dublin on Jan 18^th^ 2024 (Ethical Approval Reference Number: 211202).

### Study population, eligibility criteria and recruitment strategy

#### Study population

This study will include a non-geriatric population of women who attend Jane’s Place in Dublin city centre. These women are socially excluded, many with multiple disadvantage and complex needs and many experiencing homelessness, addiction and mental health challenges.

#### Eligibility criteria

Inclusion criteria:

➢ Adult women (18–65 years) accessing services in Jane’s Place who consent to participation.

Exclusion criteria:

➢ Any person not meeting the age eligibility criteria.➢ Any person identifying as a male.➢ Any person lacking capacity to give consent.➢ Any person with major physical/medical or cognitive challenges which would preclude ability to safely complete the assessment or➢ Any person with insufficient English language ability to give fully informed consent.➢ Women with a confirmed pregnancy.

#### Recruitment strategy

All potential participants will be provided with a participant information leaflet (PIL) detailing the purpose of the data collection, potential risks and benefits and data protection rights. Where possible a seven-day gap, between receipt of the PIL and obtaining consent, will be provided to allow people time to consider participation. However, if it is their preference to be seen at an earlier and more convenient time this will be facilitated due to the innocuous nature of the evaluation.

Once the research physiotherapist is satisfied that the participant has read and fully understands the PIL, they will proceed to obtain written informed consent. Obtaining consent will take place at the first face to face interaction with the participant prior to commencement of the assessment. The written consent informs participants that they are permitted to withdraw from the study at any time. They will be provided with their own copy of this consent form and PIL with their own signature and that of the research physiotherapist.

#### Stakeholder engagement

Recommendations from the linked LEAP II trial [17] included health education and awareness workshops preceding exercise interventions to enhance health literacy, target lifestyle behavioural change and improve retention rates. Prior to the LEAP-W programme, a number of exercise workshops will be delivered for staff and service users in Jane’s Place. Feedback from this stakeholder engagement will inform the design of the intervention.

*Primary outcome*. The primary outcome is feasibility which will be measured by recruitment numbers, retention rate, adherence to the exercise programme and protein supplement, programme acceptability and adverse events (Table 1).

**Table 1 pone.0300412.t001:** Feasibility markers.

Primary Outcome: Feasibility	Method of reporting
Recruitment Numbers	Number of eligible consenting participants who completed the initial assessment
Retention rate Sub-group retention rate	Number of return visits and the frequency of attendance • *attending at least once/week for > 50% of the duration of the programme (regular attenders)* • *attending at least once/week for < 50% of the duration of the programme (sporadic attenders)* • *did not return following initial assessment (non-attenders)*. • *attendance by chronological age*, *and pre- and post-menopausal status*.
Adherence rate *(*to the exercise intervention)	Percentage of sessions adhered to/completed by participants
Adherence rate (to the nutritional supplement)	Percentage of participants who consumed the protein supplement drink
Adverse events	An unfavourable and unintended sign, symptom, or disease having been absent at baseline, or, if present at baseline, appears to worsen and is temporally associated with medical treatment or procedure, regardless of the attribution [26]
Programme Acceptability	Participant feedback provided by Exit Interviews.

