The intervention will be delivered by two research physiotherapists who will adhere to all safety procedures. Flexibility will be facilitated with the provision of a four-week window for pre-intervention evaluations prior to commencement of the programme. Using a trauma-informed lens [46] flexibly arranged group or one-to one sessions will be delivered based on participant preference. Exercise programming strategies and variables are based on our earlier work (LEAP-I and LEAP-II trials) [16, 17] and also informed by prior stakeholder involvement from people with lived experience. The exercise classes will be multi-modal, with a primary focus on strength and based on core set of resistance exercises (Table 3). Aerobic, balance and flexibility work will be integrated into the class and the exercises will be individualised based on initial assessment results and presentation of participants. Using a gender-based perspective, the following considerations and adaptions will be built into the class; (i) core-stability exercises to target pelvic floor and/or abdominal muscle weakness, (ii) bone building exercises to target peri-and postmenopausal bone loss and (iii) age-associated muscle mass loss. Music, dance and fun orientated physical activity games, an important feature of aforementioned linked studies, will be incorporated to optimize enjoyment and self-esteem. These features are incorporated to offer choice and enable empowerment in respect of a trauma informed approach, while carefully considering the exercise prescription parameters outlined above [45]. Borg’s Rate of Perceived Exertion Scale will be used to monitor effort and scale the intensity of the workout [47]. To promote post-exercise muscle protein synthesis, a nutritional supplement (200ml pre-prepared ‘protein shake’, Fresubin) which consists of 20g of protein will be offered immediately post exercise. The ‘Park Walk’ will focus on the aerobic component of the intervention, using open green space to maximise physical and mental health outcomes. It will be a flexibly arranged 20–30-minute self-paced group or one-to-one walk. To build sustainability beyond the ten-week programme brief health promoting and physical activity educational interventions will be included in the exercise class setting to empower people to engage in unsupervised exercise following the study. As per routine procedure in the centre, which incorporates frequent reminders regarding upcoming appointments or events, phone messages will be incorporated to remind participants of the weekly schedule.

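### The primary-outcome retention marker records attendance; no marker gives the share of enrolled women who reach the post-intervention assessment

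*Protocol article*

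**What the plan says.** The first objective in the Introduction is "To evaluate recruitment, retention and adherence rates, and any adverse effects of the intervention", so retention and adherence are separate quantities and both are called rates. The primary-outcome paragraph above Table 1 also lists them separately.

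Table 1 then fixes how each is reported:

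- Retention rate: "Number of return visits and the frequency of attendance".
- Sub-group retention rate, in three classes. The highest class is "attending at least once/week for > 50% of the duration of the programme (regular attenders"). The middle class is "attending at least once/week for < 50% of the duration of the programme (sporadic attenders"). The lowest class is "did not return following initial assessment (non-attenders"). Attendance is also broken down by age and menopausal status.
- Exercise adherence: "Percentage of sessions adhered to/completed by participants".
- Recruitment: the number of eligible, consenting women who completed the initial assessment.

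The second objective compares pre- and post-intervention measures, so a post-intervention assessment is already part of the design. The Introduction says of the earlier linked study that it "demonstrated high retention (83% female v 42% males"), without saying how retention was defined there. The Intervention section explains that the programme was shortened from the previous trial's 12 weeks partly to improve retention.

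**The concern.** A count of return visits and a frequency of attendance have no denominator of enrolled women and no end-of-study time point. The row labelled as a retention rate therefore does not say what proportion of women were retained. The sub-classes do yield proportions, but of how many weeks were attended, not of whether a woman was still in the study at its end.

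Two uses depend on the missing proportion. A later trial needs it to allow for loss to follow-up. It also governs how far the pre-post comparison in the second objective can be trusted, since that comparison rests on the women who are reassessed. If the regular-attender share is read as retention, either use may start from the wrong figure.

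**Working it through.** **Figures in the plan.** The plan gives no retention target to reproduce. Its one related figure, the sample size of 68, rests on adherence (60% expected, 45% minimum, 80% power). It reproduces with a one-sided alpha of 0.05 and the arcsine formula: h = 2·arcsin√0.60 − 2·arcsin√0.45 = 1.772 − 1.471 = 0.3015, and n = (1.645 + 0.842)² / 0.3015² = 68.0. Retention does not enter it.

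**Programme duration D.** The Intervention section supports two readings. It says "To build sustainability beyond the ten-week programme", which gives D = 10, and it also describes delivery over 12 weeks, which gives D = 12.

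**Applying the class rule.** Weeks attended w divided by D is compared with 50%; Table 1 sets no condition on when those weeks fall.

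| Pattern | D = 10 | D = 12 |
|---|---|---|
| Weeks 1–5, then leaves | 5/10 = 50%, no class | 5/12 = 42%, sporadic |
| Weeks 1–6, then leaves | 6/10 = 60%, regular | 6/12 = 50%, no class |
| Weeks 1–7, then leaves | 7/10 = 70%, regular | 7/12 = 58%, regular |
| Any 4 weeks, completes final assessment | 4/10 = 40%, sporadic | 4/12 = 33%, sporadic |

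The earliest permanent leaver who counts as regular stops after week 6 if D = 10, or week 7 if D = 12. She shares that class with a woman who attends to the end.

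**Overlap with adherence.** Three sessions a week for 10 weeks is 30 sessions, so return visits divided by 30 would be a session-attendance percentage. The classes are a coarser cut of the same records: six weeks at one session a week is 6/30 = 20% of sessions, six weeks at three a week is 18/30 = 60%, and both are regular.

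**Direction of the discrepancy.** Let a be the proportion of women who are regular but not reassessed, and b the proportion who are not regular but are reassessed. Then regular share − retention = a − b. The sign depends on which is larger, and the plan gives neither.

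**Illustrative size.** Suppose every woman attends weekly until permanent dropout, with a constant loss q before each week. The dropout rates are assumptions; the article gives none. For D = 10 the regular share is (1−q)⁶ and the share still attending in week 10 is (1−q)¹⁰. For D = 12 the exponents are 7 and 12.

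| q per week | D = 10: regular v attending in last week | D = 12: regular v attending in last week |
|---|---|---|
| 5% | 74% v 60% | 70% v 54% |
| 8% | 61% v 43% | 56% v 37% |
| 12% | 46% v 28% | 41% v 22% |

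With 68 women, D = 10 and q = 8%, this is 0.606 × 68 = 41 regular against 0.434 × 68 = 30 still attending in week 10. The model excludes intermittent attendance, so it can only show overstatement, and attending in the last week is only a proxy for completing the post-intervention assessment.

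**The case against.** The strongest reply is that sustained engagement is a reasonable meaning of retention in a flexible, low-threshold drop-in service. The Intervention section already describes the previous trial in terms of those who attended regularly. Under the Analytic plan the classes would be reported as frequencies and percentages, the recruitment row supplies a natural denominator, and the non-attender class captures loss straight after baseline. No retention threshold or progression rule hangs on this row.

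Much of this stands. It supports keeping the attendance classes and it limits the severity. It does not supply the missing marker, because none of the classes refers to the end of the study. The Intervention section also notes that 91% of regular attenders in the previous 12-week trial did not complete more than 10 weeks, so regular attendance and completion of the programme diverged there.

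Four stronger readings are tempting, and the document does not support them:

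- *Retention and adherence are one quantity under two names.* They share data, but the classes diverge from session percentages as shown, and the adherence wording may also cover completion within a session.
- *The retention proportion will never be produced.* Pre-post reporting would ordinarily show how many women were reassessed, and the article is condensed with a figure not shown. What can be said is that Table 1 does not name it as a marker.
- *The regular share always overstates retention.* Sporadic attenders who are reassessed push it the other way.
- *The result cannot be compared with the earlier 83%.* That study's definition is not given, so comparability is unknown, not disproved.

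**Conclusion.** The point holds as a mismatch between a named primary marker and what it measures. Table 1 reports attendance under the heading of retention rate, and no listed marker gives the proportion of enrolled women retained to the post-intervention assessment. That a woman who leaves early can be classed as regular follows from the rule itself on either reading of duration, from week 6 (D = 10) or week 7 (D = 12).

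The size is not established. On the assumed dropout model with D = 10, the regular share exceeds the share still attending in week 10 by 14 percentage points at 5% weekly loss (74 − 60) and 18 points at 12% (46 − 28). With real intermittent attendance the gap could be smaller or reversed. The sample size is unaffected and no decision rule depends on the row, so this should be fixed but is not critical.

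**What to change.** In Table 1, redefine the row as: Retention rate = women completing the post-intervention assessment / all women who completed the initial assessment. Move the present content (return visits, frequency of attendance, the regular, sporadic and non-attender classes, and the breakdown by age and menopausal status) to a separate descriptive row headed Attendance, and state there which programme duration is the denominator for the classes.

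This is a change of table wording. The second objective already requires the post-intervention assessment and the recruitment row already counts the denominator, so no new data are collected and the target of 68 stands. The one cost is that the reported retention figure may look less favourable than the regular-attender share.
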